## Abstract

**Background:**

Early and late onset post-stroke cognitive impairment (PCI) contributes substantially to disability following stroke, and is a high priority within stroke research. The aetiology for PCI is complex and related to the stroke itself, brain resilience, comorbid brain diseases, prestroke vulnerability and complications during the hospital stay. The aim of the Norwegian Cognitive Impairment After Stroke study (Nor-COAST) is to quantify and measure levels of cognitive impairments in a general Norwegian stroke population and to identify biological and clinical markers associated with prognosis for cognitive disorders following incident stroke. The study will be organised within five work packages: 1) Incidence and trajectories 2) Pathological mechanisms 3) Development of a risk score 4) Impact of physical activity and 5) Adherence to secondary prevention.

**Methods:**

Nor-COAST is an ongoing multicentre (five participating hospitals), prospective, cohort study with consecutive inclusion during the acute phase and with follow-up at three and 18 months, and at three years. Inclusion criteria are stroke defined according to the WHO criteria. During the recruitment period from 18.05.2015 to 31.03.2017, 816 participants have been included. Cognitive impairment will be classified according to the DSM-5 criteria using a consensus group. Cognitive function is assessed by a standardised neuropsychological test battery, the Montreal Cognitive Assessment, Trail making A and B, ten-word immediate and delayed recall test, the Controlled Oral Word Association, Global Deterioration Scale and proxy based information by and the Ascertain Dementia 8 item informant questionnaire. Biomarkers include magnetic resonance imaging, routine blood samples and bio-banking. Clinical assessments include characteristics of the stroke, comorbidity, delirium, frailty and tests for cognitive and physical function, sensor based activity monitoring and adherence to secondary prophylaxis.

**Discussion:**

Nor-COAST is the first Norwegian multicentre study to quantify burden of PCI that will provide reliable estimates in a general stroke population. A multidisciplinary approach aiming to identify biomarkers and clinical markers of overall prognosis will add new knowledge about risk profiles, including pre-stroke vulnerability and modifiable factors such as physical activity and secondary prophylaxis of relevance for clinical practice and later intervention studies.

**Trial registration:**

ClinicalTrials.gov: NCT02650531. Retrospectively registered January 8, 2016. First participant included May 18, 2015.

## Background

Stroke and cognitive impairment are common in old age. One in three persons will develop stroke, dementia or both [1], and the two conditions commonly coexist [2]. Impaired cognitive function contributes to the disability following stroke [3] and affects both the individual and the family and caregivers. With increased longevity and ageing population, stroke and dementia will constitute a substantial part of the disease burden in the years to come [4] with a potentially large socioeconomic gain when improving treatment and preventive strategies.

Cognitive function is therefore defined as a top priority for stroke research, especially studies of the links between cerebrovascular and degenerative disease are requested [5–7]. The term post-stroke cognitive impairment (PCI) is used to describe both mild cognitive impairment (MCI) and dementia that either become manifest three to six months after incident stroke (early-onset PCI) or develops over months and years (late-onset PCI). The observed delayed and accelerated decline in cognitive function after incident stroke suggest there is a therapeutic window for intervention and prevention of PCI [7]. Identification of biomarkers and clinical markers for risk of progression of PCI, could improve our understanding of the underlying pathological processes and help develop new strategies to reduce the burden of PCI.

### Incidence and trajectories of PCI

Reported rates for PCI varies considerably between studies. Many studies reports dementia but not MCI, and in studies that include MCI the operational definition has a large impact on the reported rate [8]. Pooled dementia rates suggest that 10% of first ever stroke survivors develop incident dementia within the first year, and 30% after recurrent stroke [9]. A Norwegian study reported an incidence of MCI and dementia one year after first ever stroke of 37.5 and 19.6%, respectively [10]. Heterogenity in reported rates of cognitive impairment following stroke can be explained by casemix differences resulting from population selection and attrition bias [6] and by varying assessment time and tools, operational definitions and diagnostic criteria [8]. Further there are few studies on the course of PCI, especially of late-onset PCI, and it is hypothesised that the course of PCI strongly depends on the underlying mechanisms [11–14]. To quantify the overall burden of PCI and explore distinct trajectories and their determinants, larger inclusive studies with longer follow-up are warranted.

### Biomarkers and predictors of PCI

A complex interplay of vascular pathology, neurodegenerative and inflammatory processes contributes to the progression of PCI [11, 14–16]. Cognitive impairment predisposes to stroke [15, 16] and patients with dementia get more severe strokes [17], supporting that the two conditions are related. Several imaging characteristics associated with PCI have been identified. Some imaging findings are more extensively studied, especially the relationship between white matter hyperintensities and cognitive impairment [18]. However, recently there has been more attention on the association between degenerative and vascular changes in the brain [2]. Chronic inflammation seems to be involved in the pathogenesis of both cerebrovascular disorders and Alzheimer’s disease. Immune activation and immune depression are present in the acute, sub-acute and chronic stage after a stroke and diminished or impaired inflammatory mechanisms are likely to be important factors in the pathways leading to dementia [19]. Cytokines are potential drivers in addition to neurovascular dysfunction, endothelial activation [20, 21] and genetic risk including Apolipoprotein Eε4 (APOE ε4) carrier status [22]. Several clinical markers are predictors of PCI, and the risk appears to increase with increasing number of predictors. Predictors include age, pre-stroke cognitive impairment, pre-stroke functioning and frailty as well as characteristics of the stroke lesion. In addition, complications in the acute and sub-acute phase as delirium, infections, falls and seizures seem to increase the risk [6].

Early and late-onset PCI is probably driven by somewhat different mechanisms, with brain resilience and characteristics of the stroke lesion being the dominant driver for early-onset PCI, while small vessel disease, Alzheimer pathology and recurrent strokes are more pronounced in late-onset PCI [11, 14, 23, 24].

### Secondary prevention, adherence and physical activity

Prevention of recurrent strokes is important in preventing PCI [6] and can probably be achieved in up to 80% by optimal secondary prevention [25]. A multi domain intervention including vascular risk monitoring and physical activity has shown to prevent cognitive decline in at-risk stroke free elderly people suggesting that secondary prevention could have an additional and independent effect on cognition and overall brain health [26]. However, guidelines for secondary prevention are rather complex, involving secondary preventive medications and healthy lifestyle including smoking cessation, moderate alcohol consumption, healthy diet and regular physical activity [27]. Adherence to both medication and lifestyle interventions have been reported to be suboptimal in many patients [28], and adherence to secondary prevention may be problematic in patients with cognitive impairment after stroke.

There is evidence that physical activity enhances cognitive function after stroke [29], and especially executive function in individuals with MCI [30]. A recent meta-analysis, representing data from 736 participants included in 14 randomized controlled trials, demonstrated a significant positive effect of physical activity on cognition post-stroke [31]. Possible mechanisms involved are reduced levels of inflammation [32], improved brain circulation, neurogenesis and increased size of hippocampus [33, 34]. On the other hand, sedentary behaviour has been identified as a risk factor for vascular disease, and hypothesized to increase the risk of cognitive impairment after stroke [35].

### Study aims

The aim of the Norwegian Cognitive Impairment After Stroke study (Nor-COAST), is to quantify and measure levels of cognitive impairments in a Norwegian general stroke cohort and to identify biomarkers and clinical markers associated with overall prognosis for early and late onset PCI.

The Nor-COAST study is organised within five work packages (WP). The aim of WP 1 is to describe incidence and distinct trajectories of PCI. In WP 2, the aim is to increase knowledge concerning the pathogenesis of early and late-onset PCI by analysing brain imaging, APOE ε4 typing and blood markers, and to explore associations between neurodegenerative disease, underlying vascular disease, inflammation and stroke characteristics. In WP 3, we aim to identify predictors for PCI in order to develop a novel risk score consisting of a few clinical markers that will enable planning of individualized prevention and treatment. The aim of WP 4 is to study the impact of physical activity and sedentary behaviour on PCI in the short and long term, and to explore associations between motor function measured by performance based tests and progression of PCI. WP 5 aims to explore the impact of cognitive function on adherence to secondary prevention and evaluate whether optimal secondary prophylaxis is protective against decline in cognitive function over time Fig. 1.

**Fig. 1 Fig1:**
[figure not shown]
Nor-COAST is organised within five work packages (WP)

## Methods/design

The Nor-COAST study is a multicentre, prospective, cohort study following participants for three years from the stroke incident. Recruitment started successively at the different sites between 18.05.2015 and 01.09.2016 and was ended as preplanned 31.03.2017, with 816 participants included. Participants were recruited from five Norwegian stroke units at the following hospitals; St. Olavs University Hospital, Trondheim (*n* = 400); Ålesund Hospital, Møre and Romsdal Health Trust, Ålesund (*n* = 33), Haukeland University Hospital, Bergen (*n* = 142); Bærum Hospital, Vestre Viken Hospital Trust, Drammen (n = 142) and Oslo University Hospital, Ullevål, Oslo (*n* = 99). All patients admitted to the participating stroke-units were consecutively screened for eligibility and approached as soon as the diagnosis was confirmed. Informed consent was given prior to data collection by the participant or by proxy if the participant lacked capacity to give informed consent. All participants received treatment and routine follow-up as usual in accordance with national and international guidelines [36, 37].

### Sample size

Based on the Norwegian stroke registry we estimated that about 1000 stroke patients in total would be available for inclusion per year in the participating hospitals. Experience from earlier studies at the same hospitals involved [10, 38] indicated that about half of eligible participants would be included and that 20–25% would be lost to follow-up during the data collection period of 18 months. With 750 patients available for follow-up, we will be able to detect an association corresponding to a correlation of 0.11 or higher (power 86% at significance level 5%). Inclusion of approximately 1000 participants would therefore be sufficient to answer the main research questions within each work package. Based on these assumptions we decided on a preplanned inclusion stop at 1000 participants or a maximum of two years inclusion period.

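### The 86% power for r = 0.11 assumes 750 followed patients; with recruitment closed at 816, the plan's own loss assumption gives 612–653 and about 78–80%

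*Protocol article*

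**What the plan says.** The Sample size section of the protocol article builds the target in four steps.

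- About 1000 stroke patients a year were thought to be available, and about half of those eligible were expected to be included.
- From earlier studies at the same hospitals, "20–25% would be lost to follow-up during the data collection period of 18 months".
- For 750 patients followed, the study will be able to "detect an association corresponding to a correlation of 0.11 or higher (power 86% at significance level 5" per cent).
- About 1000 participants are therefore judged sufficient for the main questions of every work package, and "we decided on a preplanned inclusion stop at 1000 participants or a maximum of two years inclusion period".

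The Methods/design section, immediately before it, reports that recruitment "was ended as preplanned 31.03.2017, with 816 participants included". The abstract and the Discussion also give 816. The article does not restate the power for that number, and the limitations paragraph of the Discussion does not mention the shortfall against 1000.

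**The concern.** The article reports final enrolment and, in the next section, gives a power that depends on a larger enrolment. The verb is in the future tense, so a reader can take 86% as the power of the study as it now stands. Under the plan's own loss assumption, 816 enrolled does not yield 750 followed.

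This is the only power figure in the article, and the article extends it to all five work packages. A null result for an association near r = 0.11 could be read against 86% power when the planning assumptions now support less.

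**Working it through.** **Inputs**

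| Quantity | Value | Source |
|---|---|---|
| Correlation | 0.11 | Sample size |
| Number followed | 750 | Sample size |
| Stated power | 86% | Sample size |
| Significance level | 5%, sidedness not stated | Sample size |
| Assumed loss by 18 months | 20–25% | Sample size |
| Planned enrolment | about 1000 | Sample size |
| Actual enrolment | 816 | Methods/design |

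The site counts agree with the total: 400 + 33 + 142 + 142 + 99 = 816.

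**Step 1. Reproduce the 750.** 1000 × (1 − 0.25) = 750. The plan used the pessimistic end of its loss range.

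**Step 2. Reproduce the 86%.** For a test of one correlation against zero, by Fisher's z:

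power = Φ(atanh(r) × √(n − 3) − z), with z = 1.960 for a two-sided 5% test.

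atanh(0.11) = 0.1104 and √747 = 27.33, so power = Φ(3.019 − 1.960) = Φ(1.059) = 85.5%. A noncentral t calculation gives 85.7%. A one-sided 5% test gives 91.5–91.7%, which does not match. The stated figure is therefore reproduced, and it implies a two-sided test.

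**Step 3. Apply the plan's loss to 816.**

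- 25% loss: 816 × 0.75 = 612
- 20% loss: 816 × 0.80 = 652.8, or 653

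**Step 4. Power for r = 0.11, two-sided 5%.**

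| Number followed | Fisher z | Noncentral t |
|---|---|---|
| 750 (planned) | 85.5% | 85.7% |
| 653 (816 less 20%) | 80.4% | 80.6% |
| 612 (816 less 25%) | 77.8% | 78.0% |

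By Fisher's z, power falls by 85.5 − 80.4 = 5.1 to 85.5 − 77.8 = 7.7 points.

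**Step 5. Detectable correlation.** r = tanh((1.960 + z_power) / √(n − 3)), with z_power = 1.080 for 86% and 0.842 for 80%.

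| Number followed | r at 86% power | r at 80% power |
|---|---|---|
| 750 | 0.111 | 0.102 |
| 653 | 0.119 | 0.109 |
| 612 | 0.123 | 0.113 |

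**Step 6. What it would take to keep 750.** From 816 enrolled, the allowable loss is 1 − 750/816 = 8.1%, about a third of the 25% used in planning. At the plan's loss rates, 750 followed needs 750/0.80 = 938 to 750/0.75 = 1000 enrolled.

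**The case against.** The strongest defence is that the section records how the target was set. The sentence is conditional, "With 750 patients available for follow-up, we will be able to detect", and the text around it is in planning language. Read that way, it makes no claim about 816. Nothing is hidden either: the 816, the 1000, the loss rate and the 750 are all printed, so a reader can work out the shortfall.

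Part of this stands. The arithmetic at 750 is right, and a reader who infers a calculation error would be mistaken. A planning rationale is also legitimate if it is labelled as one. Here it is not: final enrolment is already reported and the capability is still stated in the future tense, so the two sections need reconciling.

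The size is also fairly disputed. At 80% power the detectable correlation is 0.109–0.113, so the study can still detect about r = 0.11 at a conventional power. The article does not say why 0.11 matters and 0.12 does not. Incidence, trajectories and a risk score are not governed by the power of a single correlation. These points lower the severity but do not remove the inconsistency.

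A reader might also infer that closing at 816 broke the recruitment plan, since neither 1000 participants nor two full years had been reached. The documents do not support that. From 18.05.2015 to 31.03.2017 is 683 days, or 22.4 months, which lies within a limit expressed as a maximum of two years. A closing date fixed in advance inside that limit is consistent with the text. However, a time limit does not guarantee 750 followed.

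**Conclusion.** The point holds as a power figure that was not updated; it is not an arithmetic error. With 816 enrolled and the plan's assumed loss, the expected number followed at 18 months is 612–653. That gives about 78–80% power for r = 0.11, or 86% power for r of about 0.12. The severity is minor to moderate: no analysis, outcome or participant is affected, but the article's only power figure does not match its own enrolment.

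The result rests on three assumptions.

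- The test is two-sided; this is inferred from reproducing the 86%.
- The 20–25% is a planning assumption and not an observed loss, so 612–653 is an expectation. It would be wrong to read it as the number actually available.
- The loss rate covers 18 months only. Loss may be smaller at three months, and if it stayed below about 8% the 750 would be met there. It may be larger at three years, where power would then be lower still.

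**What to change.** In the Sample size section, label the 750 followed and 86% power as the planning assumption made for about 1000 enrolled, and add one sentence:

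> With 816 included and an assumed 20–25% loss by 18 months, about 612–653 would be expected at follow-up, giving about 78–80% power for r = 0.11, or 86% power for r of about 0.12 (two-sided 5%).

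The statement that recruitment closed to plan needs no change. The cost is wording and a slightly less favourable figure. No patients, data or design changes are needed.

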## Discussion

The current paper describes the protocol of the Nor-COAST study, an ongoing prospective, cohort study following 816 participants for three years after incident stroke. This will be the first study to quantify and report levels of cognitive impairment in a large Norwegian stroke cohort. The study will focus on the diagnosis, incidence and clinical entity of PCI, and provide estimates for the burden of both early and late onset PCI in a general stroke population.

The neuropsychological test battery used in the study is sensitive to the mild cognitive impairments including non-amnestic deficits [74] that are common in the stroke population. This will be among the first studies to use the DSM-5 criteria to diagnose MCI and dementia. In contrast to the ICD-10 criteria, the DSM-5 criteria do not require memory deficit for PCI diagnosis and are consistent with the VASCOG criteria for diagnosing vascular cognitive disorders [75] . Three years’ follow-up will allow study of the mechanisms for late-onset PCI for which there are currently few data.

Using registry data from the Norwegian stroke registry allow us to account for some of the methodological challenges associated with bias, drop-outs and testability in a heterogenic population [76–78]. This along with collection of proxy based information and systematic registrations of reason for missing data should be an advantage compared to many earlier studies aiming to describe the overall burden of PCI.

By neuroimaging and identification of genetic, vascular and inflammatory response-factors, we hope to achieve insight of stroke as a trigger for degenerative brain processes and the relevance of pre-existing risk factors, including brain pathologies, for development of PCI. Both results from visual and volumetric brain analyses will be used to identify MRI predictors of early or late onset cognitive impairment. The longitudinal design of Nor-COAST enables us to look for the contribution of vascular and degenerative changes to delayed onset PCI, and to study the characteristics of patients with augmented and prolonged inflammatory response.

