There are some limitations of the Nor-COAST study. Although the neuropsychological test battery contains most of the cognitive domains in the DSM 5, symptoms related to behavior and social cognition are not extensively assessed. Further, some selection bias may have occurred despite the inclusive nature of the study: potential participants may not have been included because of worse health status. Also the recommended neuropsychological battery is cited as taking up to 30 min to perform, but many patients needed longer or testing had to be abandoned. In addition, some assessments, eg the MRI study and parts of the cognitive testing, were not feasible for all participants because of severe illness or specific impairments.

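### The sample size calculation covers whole-cohort correlations at 18 months with 1000 included; it does not show sufficiency for every work package, for three years or for imaging, and 816 were included

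*Protocol article*

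**What the plan says.** The Sample size section expects about 1000 stroke patients a year at the participating hospitals, inclusion of about half of those eligible, and that "20–25% would be lost to follow-up during the data collection period of 18 months". Taking 750 people as followed, it states: "we will be able to detect an association corresponding to a correlation of 0.11 or higher". The power given for this is 86%, with alpha at 5%. From this it concludes "Inclusion of approximately 1000 participants would therefore be sufficient to answer the main research questions within each work package". Inclusion was to stop at 1000 participants or after at most two years.

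Other sections set a wider frame:

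- Methods/design describes a cohort "following participants for three years from the stroke incident" and reports that recruitment closed as planned with 816 included.
- Data collection and assessments, with Table 1, schedules visits at three months, 18 months and three years.
- The Discussion speaks of "following 816 participants for three years after incident stroke" and names the three-year follow-up as what makes late-onset mechanisms open to study.
- Neuroimaging describes the study MRI as a separate recruitment step, and the limitations paragraph of the Discussion says that "the MRI study and parts of the cognitive testing, were not feasible for all participants".

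**The concern.** One calculation is used to support a conclusion about five work packages. It has a single horizon (18 months), a single denominator (everyone followed) and a single starting number (1000). The study has a longer horizon, an imaging component with a smaller denominator, and a smaller starting number.

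At stake is how null results are read. A reader who takes the sentence at face value would treat a missing association at three years, or between an MRI marker and cognition, as backed by 86% power against r = 0.11. The article does not establish that. For the 816 included, it does not establish it at 18 months either.

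**Working it through.** **Inputs from the protocol article.** Planned inclusion 1000, loss 20–25% over 18 months, analysable n 750, r = 0.11, power 86%, alpha 5% (Sample size); 816 included and three years of follow-up (Methods/design). Not given: whether the test is one- or two-sided, the loss by three years, and the number with a study MRI.

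**Formulas** (Fisher z, two-sided alpha 0.05):

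- Power = Φ(atanh(r)·√(n − 3) − 1.960), with atanh(0.11) = 0.1104.
- Detectable r at 86% power = tanh((1.960 + 1.080)/√(n − 3)).

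**Step 1: reproduce the stated figure.** 1000 × (1 − 0.25) = 750. Power = Φ(0.1104 × √747 − 1.960) = Φ(1.059) = 85.5%; the noncentral t gives 85.7%. Both agree with 86%. A one-sided test would give 91.5%, so the calculation is two-sided. The 750 already uses the upper end of the loss range, and uses it at 18 months.

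**Step 2: the article's own figures with 816.** 816 × 0.80 = 653 and 816 × 0.75 = 612. To keep 750 of 816, loss could be at most 1 − 750/816 = 8.1%, against the stated 20–25%.

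**Step 3: three years, illustration only.** Assume that the 18-month loss repeats in the second 18 months, so that retention is 0.80² = 0.64 or 0.75² = 0.5625. The starting numbers are kept apart so that the effect of recruitment is not mistaken for the effect of the longer follow-up.

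| Case | n | Power at r = 0.11 | Detectable r at 86% power |
|---|---|---|---|
| Plan: 1000, 25% loss, 18 months | 750 | 85.5% | 0.111 |
| 816, 20% loss, 18 months | 653 | 80% | 0.119 |
| 816, 25% loss, 18 months | 612 | 78% | 0.123 |
| 1000, assumed 36% loss, three years | 640 | 80% | 0.120 |
| 1000, assumed 43.75% loss, three years | 563 | 74% | 0.128 |
| 816, assumed 36% loss, three years | 522 | 71% | 0.133 |
| 816, assumed 43.75% loss, three years | 459 | 65% | 0.141 |

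**Step 4: imaging, illustration only.** If 30–70% of the planned 750 had a usable study MRI (an assumed range), n would be 225–525, power at r = 0.11 would be 38–71%, and the detectable r at 86% power 0.20–0.13.

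Only steps 1 and 2 rest entirely on figures in the article, apart from two-sidedness, which step 1 infers. Steps 3 and 4 show direction and rough size.

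**The case against.** The strongest reply is that nothing is miscalculated and that inadequacy is not proved. The 86% reproduces. The article sets no target effect for any work package: r = 0.11 is what 750 people could detect, not an effect that must be detected. Even in the illustrations the detectable correlation stays small, at 0.12–0.14 for three years. Detailed calculations for each package belong in the analysis plans that the Statistical analysis section assigns to a statistician. The limitations paragraph already discloses that MRI was incomplete, and closing at 816 followed the preplanned stopping rule. All of this stands. It does not rescue the sentence, which asserts sufficiency for every work package and is not a detail left for later.

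A reader might infer more than the documents support, in four ways:

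- *That the study is underpowered at three years or for imaging.* Neither the three-year loss nor the MRI number is given. If loss were 20% at 18 months and 25% by three years, 750 of a planned 1000 would remain. Telephone and proxy assessment and registry data may also limit loss of outcome data.
- *That the 65–71% power is due to the longer follow-up.* Part of it comes from including 816. From 1000, the same assumed loss gives 74–80%.
- *That work package 2 as a whole, or late-onset impairment as a whole, is affected.* Work package 2 also uses APOE typing and blood markers, which the MRI limit does not touch. The Background defines late-onset impairment as developing over months and years, so 18-month data contribute.
- *That the risk score of work package 3 has too few events.* That would follow from counting dementia alone. The article's definition includes mild cognitive impairment. With the Norwegian one-year figures in the Background used as an illustration, (37.5% + 19.6%) × 612–653 gives about 349–373 events.

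**Conclusion.** The point holds as an over-broad claim, not as a calculation error. The article supports 86% power for r = 0.11 for one correlation with complete data on 750 people, which means whole-cohort analyses at 18 months if 1000 are included.

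The firm shortfall is modest: with 816 included and the article's own loss rate, power at 18 months is 78–80%, or the detectable r rises from 0.11 to about 0.12. This assumes a two-sided test, which is the reading that reproduces the stated power. For three years and for the imaging part of work package 2, the article gives no basis for a figure, so sufficiency there is unshown. The size of any gap depends wholly on a loss rate and an MRI number that have to be supplied.

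**What to change.** In the Sample size section:

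1. Limit the sufficiency sentence to whole-cohort associations at 18 months.
2. Restate n, power and detectable r for the 816 included: 612–653, 78–80%, about 0.12.
3. Reconcile the 18-month data collection period with the three-year follow-up in Methods/design and Table 1.
4. State the assumed loss by three years and the actual number with a study MRI, each with its detectable r.

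A full calculation for each work package can stay in the analysis plans. The change is a few sentences, with no extra patients and no change in conduct. The only cost is a slightly less favourable stated figure.
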